**Methods**

A feasibility cRCT will be conducted in Nepal and Nigeria to evaluate the feasibility of the e-mhGAP-IG for use in depression diagnosis and treatment. In each country, an estimated 20 primary health clinics (PHCs) in Nepal and 6 PHCs in Nigeria will be randomized to have their staff trained in e-mhGAP-IG or the paper version of mhGAP-IG v2.0. The PHC will be the unit of clustering. All PCWs within a facility will receive the same training (e-mhGAP-IG vs paper mhGAP-IG). Approximately 2-5 PCWs, depending on staffing, will be recruited per clinic (estimated 20 health workers per arm in Nepal and 15 per arm in Nigeria). The primary outcomes of interest will be the feasibility and acceptability of training, supervision, and care delivery using the e-mhGAP-IG. Secondary implementation outcomes include the adoption of the e-mhGAP-IG and feasibility of trial procedures. The secondary intervention outcome—and the primary outcome for a subsequent fully powered trial—will be the accurate identification of depression by PCWs. Detection rates before and after training will be compared in each arm.

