### Feasibility Criteria for Progression to Full Trial

The primary objective is to evaluate the feasibility and acceptability of the intervention, its implementation, and the trial procedures for the subsequent cRCT. We must establish indicators on what procedures to carry on to the full trial and where modifications should be made to study design or content. The overall feasibility and acceptability will be determined in the intervention arm by the following criteria at the end of the study to determine progression to the full trial:

- Identification of qualitative themes reporting that both PCWs and clients perceive group primary care mental health services as being acceptable, feasible, and appropriate
- Retention of at least 67% (27/40) of PCWs and patients through end line assessments
- Fewer than 15% (15/98) of missing items on outcome measures across all assessments or fewer than 15% (eg, 3/22 items on the R-DAQ) for each questionnaire with more than 10 items) or 50% (eg, 4/9 items on the PHQ-9; for each measure with 10 items or fewer) of missing items on an individual assessment.
- Presence of adverse events among fewer than 10% (4/40) of the participants and any serious adverse events.

In domains where criteria are met, we will retain the procedure for the full trial. In domains where criteria are not met, we will modify the procedures for the full trial, guided by data collected during interviews. The presence of any adverse events and/or serious adverse events will be addressed by the trial team to identify alternative strategies for the full trial and data safety monitoring committee. The number of feasibility and acceptability criteria that are not met will determine the extent of intervention and trial design modification. Ethical approval for this feasibility study was obtained from the following collaborating institutions:

- Psychiatry, Nursing, and Midwifery Research Ethics Committee, King's College London, United Kingdom (May 2020)
- University of Ibadan and University College Hospital Joint Ethics Committee, University of Ibadan, Nigeria (December 2018)
- Nepal Health Research Council for the Transcultural Psychosocial Organization Nepal (October 2020)
- WHO Ethics Review Committee, WHO, Geneva (May 2020).

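### The printed progression counts (27/40, 4/40, 15/98) do not fit the intervention arm they are applied to, and two of them miss their own limits

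*Protocol*

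**What the plan says.** All the criteria stand in the Protocol, section Feasibility Criteria for Progression to Full Trial. The section fixes where they are judged: "The overall feasibility and acceptability will be determined in the intervention arm by the following criteria". The list then contains four items:

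- Qualitative themes: interviews should show that health workers and patients alike "perceive group primary care mental health services as being acceptable, feasible, and appropriate".
- Keeping participants in the study, worded as "Retention of at least 67% (27/40) of PCWs and patients through end line assessments".
- Completeness of the data, worded as "Fewer than 15% (15/98) of missing items on outcome measures across all assessments". A separate limit holds for any single questionnaire of more than 10 items, worded as "fewer than 15% (eg, 3/22 items on the R-DAQ". Shorter measures have a limit of 50%, illustrated by 4/9 on the PHQ-9.
- Safety, worded as "Presence of adverse events among fewer than 10% (4/40) of the participants and any serious adverse events".

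Procedures are kept in domains where criteria are met and modified where they are not. The paragraph after the list says that the trial team will deal with any adverse or serious adverse event. It gives no numerical limit for serious events.

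The arm sizes are in the Methods part of the Abstract: "estimated 20 health workers per arm in Nepal and 15 per arm in Nigeria". The Participants section and the section on statistical power and sample size give 40 PCWs in Nepal and 30 in Nigeria over both arms.

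**The concern.** The section calls feasibility and acceptability the primary objective, and these bullets say how they are to be judged. Each threshold appears twice, as a percentage and as a count, so the two must agree and the count must use the denominator to which the criterion applies. Here the denominator of 40 looks like a whole-country figure for both arms, although the criteria are restricted to one arm. Two counts also sit at or above the limit they illustrate.

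Someone applying the bullets at the end of the study would have to choose between the percentage and the count, and would find that one retention count cannot be reached. The adverse event bullet also lists serious events inside a criterion to be met, and the qualitative bullet names a group service that the protocol does not otherwise describe.

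**Working it through.** **Inputs.** Limits and counts from the progression section: at least 67% (27/40); fewer than 15% (15/98); fewer than 15% (3/22); 50% (4/9); fewer than 10% (4/40). PCWs per arm from the Abstract: 20 in Nepal, 15 in Nigeria; pooled intervention arm 20 + 15 = 35. PCWs over both arms from Participants: 40 and 30.

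**Step 1: each printed count against its own limit.** Formula: count / denominator. For *fewer than p*, the largest passing count is the largest x with x/n < p. For *at least p*, the smallest passing count is the smallest x with x/n ≥ p.

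| Criterion | Printed count | Value | Limit × n | Meets limit? | Extreme passing count |
|---|---|---|---|---|---|
| Retention, at least 67% | 27/40 | 67.5% | 26.8 | yes | 27/40 |
| Missing items overall, under 15% | 15/98 | 15.3% | 14.7 | no | 14/98 (14.3%) |
| Missing items, R-DAQ, under 15% | 3/22 | 13.6% | 3.3 | yes | 3/22 |
| Missing items, PHQ-9, under 50% | 4/9 | 44.4% | 4.5 | yes | 4/9 |
| Adverse events, under 10% | 4/40 | 10.0% | 4.0 | no | 3/40 (7.5%) |

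The counts look like the percentage times n, taken to a nearby whole number. That would explain why two of them miss a strict limit.

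**Step 2: is there one reading that fits all the brackets?** If a bracket is a passing count, 15/98 and 4/40 fail. If it is an exclusive bound (fewer than 15 of 98, fewer than 4 of 40), those two give at most 14 and at most 3, which agrees with the percentages. But the same reading turns 3/22 and 4/9 into at most 2/22 (9.1%) and 3/9 (33.3%), although 3/22 and 4/9 already satisfy 15% and 50%. No single reading fits every bracket.

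**Step 3: the PCW counts in the intervention arm.**

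| Intervention-arm PCWs | 27 retained | Needed for at least 67% | 4 with adverse events | Allowed for under 10% |
|---|---|---|---|---|
| Nepal, 20 | impossible | 14 (70.0%); 13 is 65.0% | 20.0% | 1 (5.0%); 2 is 10.0% |
| Nigeria, 15 | impossible | 11 (73.3%); 10 is 66.7% | 26.7% | 1 (6.7%); 2 is 13.3% |
| Pooled, 35 | 77.1% | 24 (68.6%); 23 is 65.7% | 11.4% | 3 (8.6%); 4 is 11.4% |

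None of the three denominators is 40. The printed 4 exceeds 10% of each, and the printed 27 is either unattainable or a much stricter rule than 67%.

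**Step 4: patients.** The retention bullet also covers patients. The protocol gives screening totals (200 per arm per country per month) but no number entered into follow-up. Who is followed is described as those with a health worker diagnosis in one Patient Data section and as those screening positive in the other. As an illustration only, assume the prevalences quoted under Settings apply to 3 × 200 = 600 patients screened per arm and country after training: 600 × 0.168 ≈ 101 in Nepal and 600 × 0.055 = 33 in Nigeria, fewer if a diagnosis is also required. So 40 cannot be confirmed as a patient denominator.

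**Step 5: the two wording points, side by side.** The adverse event bullet puts serious events inside a criterion whose fulfilment means the procedure is kept. The paragraph after the list treats any such event as something to act on. The qualitative bullet rates a group service; the Study Arms and Remote Supervision sections describe the e-mhGAP-IG with remote supervision, and Aims and Objectives ties the primary objective to the e-mhGAP-IG.

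**The case against.** **The percentages govern, and they are unambiguous.** This stands for the two arithmetic slips. A strict reading already gives at most 3/40 and at most 14/98, so correcting those brackets on their existing denominators changes no threshold. A reader might compute that, at a true adverse event rate of 10%, the criterion is met with probability 42% if at most 3/40 is allowed and 63% if 4/40 is allowed, and call that the size of the error. The protocol does not support this: it requires counting 10.0% as fewer than 10%, uses the denominator of 40 that is itself in doubt, and ignores clustering by clinic.

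**The 40 may refer to patients.** The sample size section does use 40 for patients screening positive. It does not link that figure to the progression criteria, and the retention bullet names PCWs explicitly. That 40 is Nepal's PCW total is therefore an inference, but no other PCW count of 40 exists.

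**The section is not a stop/go rule.** This also stands. A reader might infer that two teams could reach opposite decisions on whether the full trial proceeds. The section says that unmet criteria lead to modified procedures, informed by interviews, and that the number unmet sets how much is modified.

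**Serious adverse events are plainly not a success condition.** The paragraph after the list makes that the likely intent, so a reader should not conclude that the protocol rewards them. The bullet still says something else and no limit is given. The documents support asking for reconciliation and no more.

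**Judging only the intervention arm is deliberate.** A reader might infer that omitting the control arm is an error. It is a design choice: the objective on recruitment and retention rates is not limited to one arm, so control-arm retention can still be reported, although no threshold attaches to it.

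**The word group is a slip.** Acceptability, appropriateness and feasibility of the mhGAP-IG and remote supervision are assessed elsewhere with dedicated scales and interviews, so the assessment itself is not lost.

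**Conclusion.** The point holds as a defect in the printed counts and wording, and it should be fixed. The main part is the denominator: for PCWs in the intervention arm, 27 retained is impossible within either country and is 77.1% of the pooled 35, while 4 with an adverse event is 20.0%, 26.7% or 11.4% against a limit of 10%. The second part is small, a single count at the boundary: 4/40 and 15/98 do not meet their own strict limits, and the notation is inconsistent with 3/22 and 4/9. The serious adverse event clause and the word group are wording conflicts with other text.

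This rests on the protocol's estimated PCW numbers (20 and 15 per arm) and on taking the stated percentages as the intended rules. The origin of 98 is not explained, so 14/98 assumes that this item total is right. For patients the documents show only that 40 is not tied to them, not what the correct number is.

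**What to change.** Keep the percentages and replace the counts, stating whether each criterion is judged by country or pooled:

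- **PCW retention, at least 67%:** at least 14/20 (Nepal), 11/15 (Nigeria) or 24/35 (pooled).
- **PCWs with adverse events, fewer than 10%:** at most 1/20, 1/15 or 3/35.
- **Missing items overall, fewer than 15%:** at most 14/98. Say once that bracketed counts are the largest that pass, which 3/22 and 4/9 already are.
- **Patients:** give retention as a percentage of those entered into follow-up, with the actual number as denominator.
- **Serious adverse events:** reconcile the bullet with the paragraph after the list. The sponsor decides the rule.
- **Qualitative criterion:** replace the reference to a group service with the service under test, that is, care supported by the e-mhGAP-IG and remote supervision.

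If actual PCW numbers differ from the estimates, recompute the counts from the percentages. Applying the retention and missing-data thresholds to the control arm as well is optional.

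The cost is rewording four bullets and reconciling one with the paragraph that follows. No participants, data or analyses are added.

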## Results

The Emilia project was funded in July 2018. Formative qualitative studies have been conducted in both countries, with results published from Nepal [64]. Data collection for the pilot feasibility cRCT began in January 2021 and is protected to be completed by March 2022. Activities have been delayed in both countries because of COVID-19.

## Discussion

The mhGAP-IG enables greater access to evidence-based mental health care by targeting nonmental health specialists (eg, primary care doctors, nurses, and community health workers) as providers. Despite its use in more than 100 countries, a WHO consultation process identified the paper format to be a hindrance to its uptake, due to the burden on PCWs to carry the guide with them during appointments, and limited availability of mental health specialists to provide support and supervision. The Emilia project aims to address these barriers to scale. The existing WHO-developed electronic mhGAP-IG v2.0 has been adapted and refined for use in Nepal and Nigeria. Through a feasibility cRCT, its impact on detection and treatment initiation for depression, one of the most common mental conditions, will be tested along with stakeholders' perceptions of its implementation and suitability for scale. Although we believe that the availability of the e-mhGAP-IG will improve the demand and usability of the mhGAP-IG, the paper version will still play a vital role in settings where access to electronic technology and/or the internet is limited. The inclusion of a new remote supervision module for the ongoing support of health workers, made available in both trial arms, will allow us to assess its feasibility, appropriateness, and acceptability, in addition to its potential impact on the success of both the paper and electronic mhGAP-IG versions.

This feasibility trial will provide initial evidence of the utility and impact of the e-mhGAP-IG and remote supervision. The study takes advantage of the availability and potential of electronic technology and will advance work to reduce the mental health treatment gap around the world.

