**Objective**

This study aims to assess the feasibility, acceptability, adoption, and other implementation parameters of the e-mhGAP-IG for diagnosis and management of depression in 2 lower-middle-income countries (Nepal and Nigeria) and to conduct a feasibility cluster randomized controlled trial (cRCT) to evaluate trial procedures for a subsequent fully powered trial comparing the clinical effectiveness and cost-effectiveness of the e-mhGAP-IG and remote supervision with standard mhGAP-IG implementation.

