### Aims and Objectives

Emilia aims to test the feasibility of an updated electronic Mental Health Gap Action Programme Intervention Guide (e-mhGAP-IG) and trial procedures for the future conduct of a large-scale trial, which would evaluate differences in depression detection between facilities using the e-mhGAP-IG versus the paper mhGAP-IG. The objectives of this feasibility study, in preparation for a future trial, include the following:

1. To evaluate the feasibility and overall implementability of primary care mental health services using the e-mhGAP-IG for training, supervision, and delivery of care (primary objective).
2. To determine recruitment and retention rates of PCWs and patients.
3. To establish the acceptability and feasibility of assessing PCW and patient outcomes.
4. To assess ethics and safety procedures using adverse event reporting.
5. To describe depression detection rates in primary health clinics (PHCs).
6. To describe depression treatment outcomes in PHCs.

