Nigeria is classified as a lower-middle-income country. It is home to the largest national population in Africa (195.9 million as of 2018) [25]. Recent research in the country estimated a 5.5% prevalence of depression [26]. However, similar to other LMICs, 85% of individuals living with a mental disorder receive no treatment [27]. Ibadan metropolis has 11 local government areas and a population of approximately 3.5 million people. The mental health services in Ibadan are primarily provided by 2 large general hospitals. There are 186 PHCs, each serving a population of approximately 10,000 people. The study will be conducted in 2 urban and 2 rural local government areas. PHCs in Nigeria are staffed by nonphysician health workers (nurses, community health officers, and community health extension workers) who provide treatment for common disorders (including depression) presenting in primary care. The country adopted the mhGAP-IG as a national program for expanding mental health services in 2013, and PHCs are among those where providers have received training in the use of the mhGAP-IG. In Ibadan, PCWs are provided with unstructured supervision by a supervisory general practitioner who typically oversees a group of 6-8 PHCs within a local government area.

The use of digital technology in both Nepal and Nigeria has seen exponential growth in recent years, with the trend expected to continue. In Nepal, mobile penetration was 133% in 2018, which is greater than 100% because most Nepalis have multiple mobile phone provider contracts [28]. In the same year, mobile penetration was estimated to be 49% in Nigeria, with a projected increase to 55% by 2025 [29]. A total of 36% of mobile phone connections in Nigeria are linked to a smartphone.

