## Study Arms

### Intervention Condition

The intervention will consist of (1) availability of the adapted e-mhGAP-IG for use on a clinic tablet, (2) participation in remote supervision and the support module developed in phase 1 for implementation in Nepal and Nigeria, and (3) training to all relevant PCWs and supervisors in the use of the adapted e-mhGAP-IG and clinical dashboard. Health care providers with enhanced mental health knowledge who have attended the training of trainers workshops for the e-mhGAP-IG and remote supervision will act as supervisors for the purpose of the study. These might include, but are not limited to, psychiatrists, mental health nurses, general physicians, senior PCWs, and counselors.

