### Control Condition

The control condition will consist of (1) availability of the paper version of the mhGAP-IG v2.0 adapted for use in Nepal and Nigeria, (2) participation in remote supervision and the support module developed in phase 1 for implementation in Nepal and Nigeria, and (3) training to all relevant PCWs and supervisors in the use of the paper version of the mhGAP-IG v2.0 and supervision from distance ([Table 1](#)). Trained specialists in the research teams within each study site will act as supervisors for the purpose of the study. Supervisors are intended to be health care providers with enhanced mental health knowledge who have attended the training of trainers workshops for the paper mhGAP-IG v2.0. These might include, but are not limited to, psychiatrists, mental health nurses, general physicians, senior PCWs, and counselors.

Table 1.

Feasibility study arm components.

| Component                                                                              | Intervention condition | Control condition |
|----------------------------------------------------------------------------------------|------------------------|-------------------|
| e-mhGAP-IG a v2.0                                                           | ✓                      |                   |
| Paper mhGAP-IG b v2.0 c                                          | ✓                      | ✓                 |
| Remote supervision and support module                                                  | ✓                      | ✓                 |
| Primary care workers' training in use and administration of the relevant mhGAP-IG v2.0 | ✓                      | ✓                 |
| Primary care workers' training in a clinical dashboard                                 | ✓                      |                   |
| Supervisors' training in relevant mhGAP-IG and remote supervision and support          | ✓                      | ✓                 |
| Supervisors' training in a clinical dashboard                                          | ✓                      |                   |

ae-mhGAP-IG: electronic Mental Health Gap Action Programme Intervention Guide.

bmhGAP-IG: Mental Health Gap Action Programme Intervention Guide.

cThe paper mhGAP-IG v2.0 will be used in intervention condition training and will be available for use as a resource throughout the study.

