## Remote Supervision

In both study arms, remote supervision will comprise an initial face-to-face meeting (where possible) and subsequent contact by voice and text messaging to discuss implementation of the mhGAP-IG (paper or e-version) and any case queries. Supervision format (eg, voice calls, video calls, messaging, group, and individual) will be agreed upon by each supervision dyad. Supervisors will be provided with training on how to set up and run supervision remotely using telephone and other common communication platforms such as WhatsApp groups before the start of the study. Training will cover issues such as building rapport, format for running supervision over a telephone, format for clinically supportive WhatsApp groups, and ensuring patient confidentiality when using remote supervision methods. PCWs will receive training on how to make the most of the remote supervision during the mhGAP-IG training. PCWs will have access to project mobile phones to facilitate remote supervision. Both PCWs and supervisors will be provided with data packages.

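### Both arms receive the new remote supervision module, so the trial cannot isolate its effect; yet the Discussion claims its impact, and the Objective and the Aims give different full-trial contrasts

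*Protocol*

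**What the plan says.** **Delivery.** Intervention Condition lists "participation in remote supervision and the support module developed in phase 1 for implementation in Nepal and Nigeria, and (3) training to all relevant PCWs". Control Condition lists the same module, together with "training to all relevant PCWs and supervisors in the use of the paper version of the mhGAP-IG v2.0 and supervision from distance". Table 1 ticks remote supervision for both arms. Remote Supervision gives one description: "In both study arms, remote supervision will comprise an initial face-to-face meeting (where possible) and subsequent contact by voice and text messaging". The supervision aid that differs is the clinical dashboard, which Table 1 assigns to the intervention arm only.

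**Impact claims.** The Discussion says that the module, "made available in both trial arms, will allow us to assess its feasibility, appropriateness, and acceptability, in addition to its potential impact" on how well each version of the guide succeeds. Its closing paragraph then says that the trial will yield initial evidence on usefulness and impact for the e-guide and for remote supervision together.

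**Full-trial contrast.** The abstract's Objective describes a later trial "comparing the clinical effectiveness and cost-effectiveness of the e-mhGAP-IG and remote supervision with standard mhGAP-IG implementation". Aims and Objectives describes one that would evaluate "differences in depression detection between facilities using the e-mhGAP-IG versus the paper mhGAP-IG".

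**Existing practice.** For Ibadan, Settings says that "PCWs are provided with unstructured supervision by a supervisory general practitioner". It does not describe current supervision of mhGAP-IG users in Nepal.

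**The concern.** To attribute an effect to remote supervision, some comparison must vary supervision while holding training and guide fixed. The arms do not provide one. A report following the Discussion would present a before-after change, which also contains training and anything else that changed over time, as evidence that the module works.

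The second problem is which trial is being prepared. Study Design says that these data will be used to power the later trial, and the abstract names identification of depression as its primary outcome. Under the contrast in Aims and Objectives, remote supervision is common to both sides. Under the Objective it appears on one side only, and the comparator would be a condition that this trial does not run. After training, the control arm is paper guide plus a newly developed module, with project phones and data packages. Its detection rate is the planning figure for one of these trials and not evidently for the other.

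**Working it through.** No figure in the protocol needs reproducing here. The check sets the arm components against the claims and asks whether the effect can be identified.

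**1. Exposure by arm.** On the clinic numbers in Participants and in the sample size section, 20 + 6 = 26 clinics all receive the module. Study Design instead gives 10 clinics per country, so 2 × 10 = 20, and again all receive it. Either way the contrast is 100% − 100% = 0.

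**2. Timing.** Patient detection is measured in the month before training and again from 3 months after it. The sample size section says that the later period follows 3 months of intensive supervision. Every detection measurement therefore has training and module both absent or both present.

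**3. Identifiability for detection.** The four arm-by-period cells are:

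| Cell | Intercept | Intervention arm | Training | Remote supervision | E-guide |
|---|---|---|---|---|---|
| Paper, before | 1 | 0 | 0 | 0 | 0 |
| E-guide, before | 1 | 1 | 0 | 0 | 0 |
| Paper, after | 1 | 0 | 1 | 1 | 0 |
| E-guide, after | 1 | 1 | 1 | 1 | 1 |

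The training and supervision columns are equal, so the computed rank is 4 for 5 parameters. Write t for training, s for supervision and e for the e-guide with its dashboard:

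- change in the paper arm = t + s
- change in the e-guide arm = t + s + e
- difference between the changes = e

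The trial can estimate e and the sum t + s, but not s. The protocol's own example, a rise from 10% to 53% in the e-guide arm, gives t + s + e = 53 − 10 = 43 points. If the paper arm rose by x, then e = 43 − x and t + s = x, and every split of x between t and s fits the data equally well. If the module acted differently with each guide, as the Discussion allows, there would be two supervision effects and neither would be estimable.

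Adding one post-training cell without the module (row 1, 0, 1, 0, 0) raises the rank to 5. What is missing is a condition, not sample size.

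**4. Worker outcomes.** Primary care workers are also assessed immediately after training, before supervision has had time to act. Change from then to 3 or 8 months mixes supervision with practice in using the guide and with loss of what was learned. It does not isolate the module either.

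**5. Full-trial contrasts side by side.**

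| Source | One side | Other side |
|---|---|---|
| Objective | E-guide and remote supervision | Standard implementation |
| Aims and Objectives | E-guide | Paper guide |
| Arms tested | E-guide, dashboard, module | Paper guide, module |

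The last two rows agree, with the module common to both sides. The first row differs.

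**The case against.** Giving the module to both arms is a sound way to compare guide formats, and that point stands. Four further points have force.

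- **Hedging.** The first Discussion sentence speaks of potential impact. The Perceptions of Supervisory Support Scale, the acceptability, appropriateness and feasibility measures, the interviews, and the planned models relating outcomes to implementation survey scores can explore how supervision was received and whether ratings track detection. This is legitimate exploratory work. But everyone surveyed has the module, so such an association is uncontrolled, and the second Discussion sentence carries no hedge.
- **Supervision is not identical.** A reader might infer that both arms are supervised in exactly the same way. The documents do not support this. The dashboard, which helps supervisors find issues to raise, is in the intervention arm only; the two arm descriptions of supervisors differ; and each dyad agrees its own format. The difference does not rescue the impact claim, because the dashboard's effect belongs to the e-guide package.
- **Preparation of the full trial.** A reader might infer that the trial cannot prepare the study named in the Objective. That goes too far. The progression criteria rest on qualitative themes, retention, missing items and adverse events in the intervention arm, and none uses a control detection rate. Recruitment, retention and measurement can be piloted whatever the later comparator is.
- **Misuse of control figures.** A reader might infer that the protocol plans to use the control rate as a standard-implementation rate, or that its costs are contaminated. No section states the first. On costs, supervision time is collected as a separate component, and the economic model compares the e-guide with the paper tool. The pre-training month in Nigeria, where mhGAP-IG was already adopted, may also approximate existing practice.

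The Objective does not define standard implementation, and the abstract's Methods names the paper version as this trial's comparator. Unstructured general-practitioner supervision is described for Ibadan only, while 20 of the 26 clinics are in Nepal. That makes the Objective ambiguous; it does not bring it into line with Aims and Objectives.

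**Conclusion.** The point holds in a bounded form. Both Discussion statements on the impact of remote supervision go beyond the design: between-arm exposure contrast is zero, and the module cannot be separated from training in the detection data at any sample size. This rests on the module reaching all clinics and starting with training, as the arm descriptions and the sample size section indicate. The Objective and the Aims also describe different full-trial contrasts, and only the Aims version corresponds to the arms tested.

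Feasibility, appropriateness and acceptability of remote supervision, and perceived support, remain assessable. The randomised comparison of e-guide with dashboard against paper guide is untouched. The consequence is for what may be concluded and for how control-arm detection is carried into planning, not for the validity of the trial's conduct.

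**What to change.** 1. In both Discussion sentences, limit the claim about remote supervision to feasibility, appropriateness and acceptability. Describe any link between supervision measures and detection as exploratory and uncontrolled. Changing only the first sentence would leave the unhedged one in place.
2. Reconcile the Objective with Aims and Objectives. The choice is the sponsor's: either state the full-trial contrast as e-guide with dashboard versus paper guide, both with remote supervision; or keep the Objective's contrast, define standard implementation for each country, and state that this trial's control arm does not pilot it.
3. When post-training control-arm detection is used to plan the full trial, label it as paper guide plus remote supervision module.

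The cost is a protocol wording change and a narrower stated conclusion. Arms, sample size, data collection and progression criteria stay as they are. If the module's own effect is a target, it needs a comparison condition without the module, which would be a design decision for a later trial.
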